#### **9.1.7 Reporting procedures for SAEs**

In case of a serious Adverse event, the Investigator has to use all supportive measures for best patient treatment. A written report is also to be prepared and should at least contain the following:

- Patient number
- Patient: sex
- The suspected investigational medical product (IMP)
- The adverse event assessed as serious
- Short description of the event and outcome

If applicable, the initial report should be followed by the Follow up report, indicating the outcome of the SAE.

### 9.1.8 Reporting procedures for SUSAR

It must be remembered that the regulatory authorities, and the Institutional Review Board / Independent Ethics Committee (IRB / IEC) must be informed about all SUSAR. Such reports shall be made by the sponsor and should content at least the following details:

- Patient number (study code/screening number)
- Patient: age in years, sex
- Name of Investigator and investigating site
- Period of administration
- The suspected investigational medical product (IMP)
- The adverse event assessed as serious and unexpected, and for which there is a **suspected** causal relationship to the IMP
- Concomitant disease and medication
- Short description of the event:
  - Description
  - Onset and if applicable, end
  - Therapeutic intervention
  - Causal relationship
  - Seriousness criteria or reportable reason

Electronic reporting should be the expected method for reporting of SUSARs to the competent authority. In that case, the format and content as defined by the regulatory requirements should be adhered to. The latest version of MedDRA should be applied. Lower level terms (LLT) should be used.

### **9.1.9 Development Safety Update Report**

A Development Safety Update Report (DSUR) will be provided by the Sponsor annually. This report will also be presented annually to the Independent Ethics (IEC) and to the competent authorities by the sponsor.

## **10. FOLLOW-UP**

### **Follow-up of study participants including follow-up of adverse events**

Patients will be at the hospital at least two days after surgery (surgery = day 1). During this time patients will be asked for any adverse events on a daily basis. Additionally, patients will be followed up one week after surgery for wound inspection and stitch removal. At this follow-up visit patients will be asked for adverse events as well.

### **Treatment after end of study**

There will be no treatment after end of study.

## **11. STATISTICAL METHODOLOGY AND ANALYSIS**

### **Statistical methodology**

#### Primary objective:

The paired t-test will be used to compare the log-transformed perilymphatic and blood concentrations of Triamcinolone acetonide, and a 95% confidence interval will be calculated for the geometric mean ratio.

#### Secondary objective:

Descriptive statistical methods will be used for the secondary (hypotheses generating) objective to compare the 4 groups of patients. Perilymphatic and blood concentrations of

Triamcinolone acetonide of the 4 groups will be graphically presented by boxplots, both on the original and on the log-transformed scale. Median (quartile) concentrations and means  $\pm$  standard deviations of the log-transformed concentrations will be calculated.

## **Data handling**

Case report forms will be copied and stored separately. Data will be double-checked and saved in an excel sheet on a computer to which only study personnel has access to. Patients will be randomly assigned a three-digit number and the further data analysis will be carried out anonymously.

## **Analysis sets**

### **Intention to treat set**

This analysis set includes subjects who were randomized (and received at least one dose study drug).

### **Sample size considerations**

The sample size calculation is based on the paired t-test and a two-sided significance level of 5%. Perilymphatic and blood concentrations of 12 patients are known from the literature (Bird et al, 2011) with geometric mean values of 1.26 and 0.001, respectively, and the standard deviation of the paired differences of the log10-transformed values was calculated as 0.81. To detect an effect size of 0.5 standard deviations, which is a difference of 0.4 on the log-scale (a difference in the geometric means of 1.26 to 0.5) with a statistical power of 86%, a total number of 40 patients have to be included in the study (nQuery Advisor 7.0).

### **Relevant protocol deviations**

All protocol deviations will be listed in the study report and noted on case report forms.

## **Endpoints analysis**

### **11.1.1 Primary endpoint analysis**

Perilymphatic and blood concentration of Triamcinolone acetonide

#### Primary objective:

The paired t-test will be used to compare the log-transformed perilymphatic and blood concentrations of Triamcinolone acetonide, and a 95% confidence interval will be calculated for the geometric mean ratio.

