## 7. STUDY DESIGN

At the ENT department of the university hospital Vienna (AKH Wien) patients are treated with intratympanic triamcinolone acetonide before cochlea implantation to reduce inflammation and in some cases to protect residual hearing. Triamcinolone acetonide levels in cochlear perilymph will be evaluated in an open prospective clinical study. Patients scheduled for cochlear implant surgery between 18 and 90 years will be included. Patients who are treated with steroids preoperatively will be excluded from the study. Patients will be randomized after inclusion to one of four groups. The randomization is carried out to generate hypothesis for the needed dose and best time of application in the future. Triamcinolone acetonide will then be applied 20-24h before surgery or at the beginning of the surgery, depending on randomization (see below). About 20 µl of perilymph will be sampled simultaneously to a

blood sample during cochlear implant surgery. The first twenty patients will be randomized to Triamcinolone acetonide 40mg to allow for a first analysis of the samples. Patients 21 to forty will be randomized to Triamcinolone acetonide 10mg.

The probes will be stored at -80°C. Triamcinolone acetonide levels of the blood and perilymph will be determined by the pharmaceutical laboratory (Department of Pharmaceutical Technology and Biopharmaceutics, University of Vienna).

The patients will be randomized to 4 groups. Group 1 - Volon A® 10mg administration 20 - 24 hours before sampling. Group 2 – Volon® A 40mg administration 20 - 24 hours before sampling. Group 3 Volon® A 10mg – administration 1 to 2 hours before sampling. Group 4 – Volon A® 40mg administration 1 to 2 hours before sampling.

The time interval of application (1 to 2 hours and 20 to 24 hours before sampling) are a result of varying time of surgery depending on surgeons and patient anatomy as well as day to day clinical organization. Patients can withdraw consent at any time of the study.

The active phase of each patient will be between 6 and 9 days depending on time of follow-up visit.

[figure not shown]

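### The primary paired t-test pools four dose-by-time groups; adding group as a factor would protect the stated 86% power and the confidence interval at almost no cost

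*Protocol*

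**What the plan says.** The synopsis, the opening of section 11 and section 11.1.1 all give the same primary analysis: "The paired t-test will be used to compare the log-transformed perilymphatic and blood concentrations of Triamcinolone acetonide", with a 95% confidence interval for the geometric mean ratio. None of them contains a term for group, dose or time.

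The sample size paragraph of section 11 sizes this test on the whole trial: "with a statistical power of 86%, a total number of 40 patients have to be included in the study". Its target is stated as "To detect an effect size of 0.5 standard deviations, which is a difference of 0.4 on the log-scale". It uses a single SD of the paired log10 differences, derived from 12 literature patients ("transformed values was calculated as 0.81"). One test with one SD on the full 40 can only mean that the groups are pooled, although the word is not used.

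The 40 are not one regimen. Section 7 says "The patients will be randomized to 4 groups". They are 10 mg or 40 mg, given 1 to 2 hours or 20 to 24 hours before sampling, and section 8.2 gives 10 patients to each. The groups are used only in the descriptive secondary analysis (11.1.2). That analysis covers perilymph and blood concentrations by group and names no within-patient ratio with a confidence interval per group.

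**The concern.** A one-sample paired t-test treats every departure of a patient's log ratio from the overall mean as random error. Here part of that departure may be systematic, because dose and sampling time are fixed by design and the trial was set up to learn how they matter. If the perilymph/blood ratio differs between the four cells, the estimated standard error is too large, the confidence interval for the primary ratio is wider than it need be, and power falls below the figure planned.

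A separate point concerns interpretation. The primary objective is uptake into perilymph compared with spread to blood. A single ratio averaged over two doses and two sampling times is not specific to any regimen, and no regimen-specific ratio with an interval is named elsewhere.

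**Working it through.** **Inputs from the protocol.** Two-sided 5% paired t-test; difference 0.4 log10; SD 0.81; n = 40; four cells of 10. Group 5 in the synopsis lies outside the 1:1:1:1 allocation and is left out. No dropout allowance is stated, so none is applied.

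**1. The plan's own figure.** Noncentral t with 39 df and noncentrality (0.4/0.81) × √40 = 3.12 gives power 86.1%. Using 0.5 SD exactly gives 86.9%. The stated 86% reproduces.

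**2. What pooling does to the error term.** Let the cell means of d = log10(perilymph) − log10(plasma) lie at 0.4 + mⱼ, where the mⱼ average to zero, and let the within-cell SD be 0.81. Because the cell sizes are fixed, the true standard error of the overall mean stays at 0.81/√40 = 0.128. The pooled test instead estimates it from a variance with expectation

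0.81² + (40/39) × mean(mⱼ²).

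For an early/late difference of k-fold in the ratio and no dose difference, mⱼ = ± log10(k)/2.

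- k = 3: mⱼ = ±0.239; variance 0.656 + 0.058 = 0.714; SD 0.845.
- k = 10: mⱼ = ±0.5; variance 0.656 + 0.256 = 0.912; SD 0.955.
- k = 30: mⱼ = ±0.739; variance 0.656 + 0.560 = 1.216; SD 1.103.

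**3. Effect on power, coverage and width.** Simulation of 200,000 trials per row, true mean difference 0.4. The fold differences are assumptions; the protocol gives none.

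| Early/late difference in ratio | Pooled power | Pooled 95% CI coverage | CI width against model with group |
|---|---|---|---|
| none | 86% | 95% | equal |
| 3-fold | 84% | 95.9% | +4% |
| 10-fold | 77% | 97.9% | +18% |
| 30-fold | 64% | 99.2% | +36% |

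Adding an assumed 4-fold difference in the ratio between doses to the last three rows gives power of about 81%, 73% and 61%. With group as a factor (36 residual df), power is about 86% and coverage about 95% in every row. With no group differences at all, the factor costs 0.1 point: 86.0% against 86.1%.

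**4. At the literature contrast.** The sample size paragraph cites 12 patients "with geometric mean values of 1.26 and 0.001, respectively". log10(1.26/0.001) = 3.10, and 3.10/0.81 = 3.83 SD. For power to fall to 86% at a difference of 3.10, the pooled SD would have to reach about 3.10 × 0.81/0.4 = 6.3. None of the scenarios comes near that, so power is essentially 100% in all of them.

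**5. One group alone.** With n = 10, power at 0.4 log10 is 29%; at 3.10 log10 it exceeds 99.9%.

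**The case against.** The strongest reply is that the protocol's figure is right and that the loss rests on numbers it does not contain. That stands. A reader might infer from the pooling that the trial does not have its stated 86% power. The documents do not support this, for four reasons.

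- The figure reproduces from the stated inputs.
- Only a difference in the perilymph/blood *ratio* matters. A dose effect that scales both fluids alike cancels in the paired difference, and the protocol states no expected group difference in the ratio.
- The protocol does not say whether the 12 literature patients shared one regimen and sampling time, so 0.81 may already contain some of this spread.
- The loss passes about 2 points only once the between-group SD of the log ratio exceeds roughly 0.2 to 0.25 log10.

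A reader might also infer that the test is invalid. It is not. Coverage is at or above 95%, so the type I error is at or below 5% and the fault is on the safe side.

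It can further be said that the proposed primary estimate describes no single regimen either. That is correct: with 10 per cell, the equally weighted mean of the cells is numerically the pooled mean. The factor repairs the interval, and only the group-specific ratios address interpretation.

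Finally, by-group means of log perilymph and log blood are already planned, and each group's ratio follows from their difference. Its interval does not, because SDs of the two fluids reported separately do not give the SD of the paired difference.

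**Conclusion.** The primary analysis leaves the trial's own design groups out of its error model. The 86% is correct as computed and conditional in what it promises: it holds if the log ratio does not vary between groups beyond the SD of 0.81. Under assumed 3-, 10- or 30-fold early-versus-late differences in the ratio, power at the design difference of 0.4 log10 is about 84%, 77% or 64%. If the true contrast is close to the cited literature one, power is near 100% throughout and what remains is a wider interval than necessary, by about 4%, 18% or 36% in the same scenarios. The point is therefore a free improvement to a stated method. It is not an error in the stated power and not a threat to the validity of the test.

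**What to change.** In the synopsis, the opening of section 11 and section 11.1.1, replace the single paired t-test with a linear model for d = log10(perilymph) − log10(plasma), with the four groups (dose by time) as a factor.

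- **Primary estimate:** the equally weighted mean of the four cell means, tested against zero on 36 df and back-transformed to a geometric mean ratio with its 95% confidence interval. With equal cells the point estimate is the same as in the pooled test.
- **Beside it:** the four group-specific geometric mean ratios with paired 95% confidence intervals. Label these as estimates and not as separate primary tests, given 29% power per group at 0.4 log10.
- **Sample size paragraph:** state that the 86% assumes a within-group SD of 0.81.

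The cost is wording, three degrees of freedom and 0.1 point of power (86.1% to 86.0%). No further patients, samples or assays are needed.

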### **11.1.2 Secondary endpoint analysis**

#### **Secondary objective:**

Descriptive statistical methods will be used for the secondary (hypotheses generating) objective to compare the 4 groups of patients. Perilymphatic and blood concentrations of Triamcinolone acetonide of the 4 groups will be graphically presented by boxplots, both on the original and on the log-transformed scale. Median (quartile) concentrations and means  $\pm$  standard deviations of the log-transformed concentrations will be calculated.

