### Secondary Objectives (Hypothesis)

Assess the stability of triamcinolone acetonide levels in the cochlear perilymph.

Assess the difference of triamcinolone acetonide levels in the cochlear perilymph and blood after administration of different doses of Triamcinolone acetonide.

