## **8.4 Benefit and risk assessment**

This study consists of a perilymph and a blood sample during cochlear implantation. Patients included in the study are deaf or profoundly hearing impaired. As previously shown in other studies sampling of the perilymph is a safe method.

This study can give us information on the absorption of Triamcinolone acetate by perilymph as well as information on the stability of Triamcinolone acetate after absorption of the perilymph. Since Triamcinolone acetate is used in the treatment of sudden SNHL and preoperatively, this study can deliver necessary information on the best timing of drug application and the necessary dose.

Additionally, a blood sample is taken, which can lead to known risks such as infections and hematoma.

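### The secondary analysis summarises each group separately, so stability and the dose difference get no planned ratio or interval, and the randomised timing comparison is never estimated

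*Protocol*

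**What the plan says.** Section 6 sets two secondary objectives. One is to "Assess the stability of triamcinolone acetonide levels in the cochlear perilymph". The other is to assess how perilymph and blood levels differ between doses.

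The analysis appears in the synopsis, at the start of section 11 and in 11.1.2, in matching terms: "Descriptive statistical methods will be used for the secondary (hypotheses generating) objective to compare the 4 groups of patients". The listed outputs are boxplots on the original and log scales, medians with quartiles, and means ± SD of the log concentrations. No between-group ratio, interval, or pooled time or dose effect is named, and stability has no definition. The only planned confidence interval is for the perilymph-to-blood geometric mean ratio of the primary objective (11.1.1).

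Table 1 schedules one perilymph and one blood sample per patient. Sections 7 and 8.2 give 40 mg to the first twenty patients and 10 mg to the next twenty. Section 8.2 randomises each patient on day 0 to one of two groups, which settles whether the drug is applied 20–24 h or 1–2 h before sampling. The same section also speaks of equal allocation across four groups, 10 patients each.

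Section 8.4 says that "this study can deliver necessary information on the best timing of drug application and the necessary dose".

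**The concern.** An objective worded as a difference should produce an estimate of that difference. With one sample per patient, nothing is observed within a patient over time. Stability is therefore a between-patient ratio of 24 h to 1 h concentrations, and it cannot be read from a single group's summary. The plan stops at the single groups.

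This matters most for the depot question. The study rationale in section 5 says that a depot effect is presumed and that longer-lasting perilymph levels are unproven. A depot claim is a claim of little decline, and with 10 patients per group a substantial decline can leave the two boxes overlapping. Without a stated ratio and interval, the report need not show how large a fall the data still allow. Section 8.4 expects the results to inform timing and dose, so that precision should be visible.

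**Working it through.** **1. The plan's own figure.** Inputs from Sample size considerations in section 11: "The sample size calculation is based on the paired t-test and a two-sided significance level of 5" per cent; "To detect an effect size of 0.5 standard deviations, which is a difference of 0.4 on the log-scale"; the SD of paired log10 differences, whose "transformed values was calculated as 0.81"; "with a statistical power of 86" per cent; and "a total number of 40 patients have to be included in the study".

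d = 0.4/0.81 = 0.494. The noncentrality is 0.494 × √40 = 3.12 on 39 df. The exact two-sided paired-t power is 86.1% (86.9% if d is taken as 0.5). The stated figure reproduces. It covers the paired primary test only and says nothing about comparisons between groups.

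**2. Precision of group comparisons.** The between-patient SD of log10 perilymph concentration is not given, so it is assumed. The 0.81 is the SD of perilymph-minus-blood differences for a different drug and serves only as a stand-in. The value 0.57 is 0.81/√2, which would hold if the two fluids had equal SDs and were uncorrelated. The wider range is 0.3 to 1.0.

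- 10 v 10: half-width = t(0.975, 18) × SD × √(2/10), with t = 2.101
- 20 v 20: half-width = t(0.975, 36) × SD × √(2/20), with t = 2.028
- timing-by-dose interaction: half-width = t(0.975, 36) × SD × √(4/10)

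At SD 0.81 the 10 v 10 half-width is 2.101 × 0.81 × 0.447 = 0.761, and 10^0.761 = 5.8. The 20 v 20 half-width is 2.028 × 0.81 × 0.316 = 0.519, and 10^0.519 = 3.3.

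| Assumed log10 SD | 10 v 10: half-width, factor | 20 v 20: half-width, factor | Interaction: half-width, factor |
|---|---|---|---|
| 0.3 | 0.282, ×/÷ 1.9 | 0.192, ×/÷ 1.6 | 0.385, ×/÷ 2.4 |
| 0.4 | 0.376, ×/÷ 2.4 | 0.257, ×/÷ 1.8 | 0.513, ×/÷ 3.3 |
| 0.57 | 0.536, ×/÷ 3.4 | 0.366, ×/÷ 2.3 | 0.731, ×/÷ 5.4 |
| 0.81 | 0.761, ×/÷ 5.8 | 0.519, ×/÷ 3.3 | 1.039, ×/÷ 10.9 |
| 1.0 | 0.940, ×/÷ 8.7 | 0.641, ×/÷ 4.4 | 1.283, ×/÷ 19.2 |

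Pooling narrows the log-scale interval by about 30% (at SD 0.81, 1 − 0.519/0.761 = 0.32).

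**3. What the eye would see.** Two groups of 10 were simulated 40,000 times on the log10 scale. The table gives the share of trials in which the interquartile boxes overlap, and the two-sided 5% power to detect a fall.

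| | SD 0.4 | SD 0.57 | SD 0.81 |
|---|---|---|---|
| Boxes overlap, true 2.5-fold fall | 62% | 80% | 89% |
| Boxes overlap, true 4-fold fall | 27% | 58% | 78% |
| Power, 0.4 log10 (2.5-fold) fall, 10 v 10 | 56% | 32% | 18% |
| Power, 0.4 log10 (2.5-fold) fall, 20 v 20 | 87% | 58% | 33% |
| Power, 5-fold fall, 10 v 10 | 96% | 74% | 45% |
| Power, 5-fold fall, 20 v 20 | >99% | 97% | 76% |

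**4. Which contrast is randomised.** In the sequence of sections 7 and 8.2, timing is randomised within each block of twenty, and dose is fixed by position in the enrolment order. The pooled 24 h:1 h ratio, with dose half as a factor, therefore rests on randomisation. The 40:10 mg ratio compares patients 1–20 with patients 21–40, so any drift in patients, surgery, sampling or assay falls wholly on it. Adjusting for sampling time does not remove that.

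**The case against.** The secondary objective is openly hypothesis generating, and section 7 gives the same purpose for the randomisation. A descriptive analysis does not contradict that, and no hypothesis test is owed. Model details are also commonly left to a statistical analysis plan, which is not shown here. This stands in so far as no test or power calculation should be demanded. It does not dispose of the point: the protocol itself fixes the secondary analysis, three times in matching terms, and that list does not estimate the objectives. An interval is itself a description of precision and suits an exploratory label.

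The plan is also more than boxplots and medians. Log-scale means and SDs are planned, and with the group sizes a reader could work out any ratio and interval. So no information is lost; what is missing is a commitment to report the estimate.

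Three stronger readings are tempting, and the protocol does not support them:

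- *Stability will be judged from overlapping boxes.* No section says so. The plan leaves that risk open but states no such rule.
- *A 5-fold decline could not be told from stability.* At SD 0.81 an observed 5-fold ratio in 10 v 10 would have an interval including 1 (log10 5 = 0.70 < 0.761). A true 5-fold decline would still be detected with about 45% power, and with 96% at SD 0.4.
- *The trial is a randomised 2×2 factorial whose dose effect is being discarded.* The wording in 8.2 on equal allocation to four groups may suggest this, but the enrolment sequence stated in sections 7 and 8.2 does not allow it.

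**Conclusion.** The point holds as a gap in estimation. Section 11.1.2 limits the secondary analysis to per-group summaries, so neither secondary objective gets a planned ratio or interval, and the randomised timing comparison is not estimated. It is worth correcting but does not threaten the primary analysis, whose power calculation reproduces.

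For assumed SDs of 0.4 to 0.81, a single 10 v 10 ratio is known only to within ×/÷ 2.4 to 5.8, against ×/÷ 1.8 to 3.3 when pooled. These widths rest on an assumed between-patient SD, log-normal concentrations, and complete data in 10 patients per group. The gap itself depends on none of them.

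The pooled ratio has a limit: it describes both doses only if the decline is similar in each. The trial can check that only weakly, with an interaction factor of about ×/÷ 3.3 to 10.9 over the same SDs.

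**What to change.** In 11.1.2, and in the two places that repeat it:

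- Keep the boxplots, medians with quartiles, and log-scale means ± SD.
- For log perilymph and log plasma separately, add the 24 h:1 h geometric mean ratio with 95% CI, within each dose and pooled with dose half as a factor (20 v 20). Label these exploratory and show the within-dose ratios beside the pooled one.
- State that stability is described by this ratio and its interval and is not inferred from overlapping boxes or a non-significant difference.
- Report any 40:10 mg ratio, with its interval, only as a non-concurrent comparison, and say that dose follows enrolment order.
- Bring the section 8.4 statement on timing and dose into line with the hypothesis-generating label.

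The cost is a few lines of text and analysis. It needs no new data or patients, and no multiplicity adjustment while the estimates stay exploratory. The method is already in the protocol, since 11.1.1 uses a geometric mean ratio with a 95% CI for the primary objective.
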